### 2.2. Assessment Schedules

General anamnesis, ergospirometry, body composition, physical activity level, and dietary intake measurements.

A general anamnesis will be taken, including sociodemographic characteristics, lifestyle habits, and self-rated health and medical history (family comorbidities, cardiopulmonary symptoms, and medication use). The questions in each medical domain are designed to allow self-rated assessments of pre-COVID-19 symptoms; symptoms that emerged during acute COVID-19; and persistent symptoms. The interview will also include the Medical Research Council (MRC) Dyspnoea Scale [30], the short form of the International Physical Exercise Questionnaire [31], and COVID-19 quality of life score by Post-COVID-19 Functional Status Scale [32].

All subjects will complete a peak oxygen uptake (VO2peak) protocol. Oxygen uptake will be measured with an incremental protocol on a friction-loaded cycle ergometer (Lode Excalibur, Groningen, The Netherlands) with expired gases analyzed using a breath-by-breath automated gas-analysis system (Quark CPET Cosmed, Rome, Italy). Stature will be measured on a fixed stadiometer (Sanny, São Paulo, Brazil) with an accuracy of 0.1 cm and a length of 2.20 m. Bodyweight will be measured using an electronic scale (FilizolaPL50, Filizola Ltd.a., São Paulo, Brazil) with a precision of 0.1 kg.

Body composition (total fat mass, trunk fat mass, abdominal fat, and lean mass) will be analyzed by ultrasonography using a 3.5-MHz probe located 1 cm from the umbilicus. Two ultrasonography measurements of visceral adipose tissue will be defined as the distance between the internal face of the same muscle and the anterior wall of the aorta. All measurements will be expressed in absolute and percentage values. Participants will be grouped into those with low-visceral adipose tissue (values below 3 ± 1 cm) and those with high-visceral adipose tissue (values above 5 ± 1 cm). Also, body composition (body mass, fat mass, musculoskeletal, bone, and fat-free mass from upper and lower limbs and trunk) will be analyzed using DXA (model DPX-MD, software 4.7, General Electric Healthcare, Lunar DPX-NT; Little Chalfont, Buckinghamshire, United Kingdom). Impedance measurements will be taken using a phase-sensitive bioimpedance analyzer (Bia Vitality, Harrisville, NH, USA) at a frequency of 50 kHz. Bioimpedance parameters [Resistance (R) and reactance (Xc)] were analyzed based on the BIVA procedures [33]. Phase angle will be calculated as the arctangent of Xc/R*180°/π. Total, intra- and extracellular water, body cell, and muscle mass will be estimated using specific bioimpedance-derived equations [34,35,36].

Nutritional information will be recorded at the initial screening from three-day food diaries that will be filled over two weekdays and one weekend day to better reflect typical intakes. Participants will meet with a nutritionist before testing and they will be instructed on how to complete the food diaries. Total energy, protein, carbohydrates, and fat intake will be analyzed using NutWinsoftware, version 1.5.

Physical activity levels will be measured using a triaxial accelerometer (GT3X+; ActiGraph, LLC, Pensacola, FL, USA) which gives valid estimates of physical activity in controlled and free-living environments. Participants will use an accelerometer worn above the waist for seven consecutive days during waking hours. A minimum of four days with at least 10 h/day will be defined as valid accelerometer data. Participants will be instructed not to use the accelerometer while bathing or performing water activities. Each day, participants will be responsible for recording when they went to sleep, when they woke up, and whether or not they took off the device. The data will be processed using the ActLife software version 6.9.2 (Pensacola, FL, USA).

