## Abstract

**Background:** This proposal aims to explain some of the gaps in scientific knowledge on the natural history of coronavirus disease (COVID-19), with a specific focus on immune, inflammatory, and metabolic markers, in parallel with temporal assessment of clinical and mental health in patients with COVID-19. The study will explore the temporal modulatory effects of physical activity and body composition on individual trajectories. This approach will provide a better understanding of the survival mechanisms provided by the immunomodulatory role of physical fitness. **Methods:** We will conduct a prospective observational cohort study including adult patients previously infected with the SARS-CoV-2 virus who have expressed a mild to moderate COVID-19 infection. Procedures will be conducted for all participants at baseline, six weeks after vaccination, and again at 12 months. At each visit, a venous blood sample will be collected for immune phenotypic characterization and biochemistry assays (inflammatory and metabolic parameters). Also, body composition, physical activity level, cardiovascular and pulmonary function, peripheral and respiratory muscle strength, functional exercise capacity, and mental health will be evaluated. Using the baseline information, participants will be grouped based on physical activity levels (sedentary versus active), body composition (normal weight versus overweight or obese), and SARS-CoV-2 status (positive versus negative). A sub-study will provide mechanistic evidence using an in-vitro assay based on well-trained individuals and age-matched sedentary controls who are negative for SARS-CoV-2 infection. Whole blood will be stimulated using recombinant human coronavirus to determine the cytokine profile. Peripheral blood mononuclear cells (PBMCs) from healthy well-trained participants will be collected and treated with homologous serum (from the main study; samples collected before and after the vaccine) and recombinant coronavirus (inactive virus). The metabolism of PBMCs will be analyzed using Respirometry (Seahorse). Data will be analyzed using multilevel repeated-measures ANOVA. **Conclusions:** The data generated will help us answer three main questions: (1) Does the innate immune system of physically active individuals respond better to viral infections compared with that of sedentary people? (2) which functional and metabolic mechanisms explain the differences in responses in participants with different physical fitness levels? and (3) do these mechanisms have long-term positive modulatory effects on mental and cardiovascular health? Trial registration number: Brazilian Registry of Clinical Trials: RBR-5dqvkv3. Registered on 21 September 2021.

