Considering the previous rationale and the current pandemic, it is imperative to ask: What are the long-term consequences of COVID-19 and how do physical activity, body composition, immune profiles, and inflammation contribute to different trajectories of general clinical functions throughout a lifetime and overall physiological recovery? There is no data on the prevalence, nature, and behavior of COVID-19 in physically active individuals, and little is known about the long-term health consequences of COVID-19 and its relation with SARS-CoV-2 vaccination [28].

This proposal describes methods for an observational prospective follow-up investigation of adult patients previously infected with mild to moderate COVID-19, we will conduct measures 3 times, (1) baseline, (2) six weeks after full vaccination, and (3) again at 12 months. Investigations of this magnitude in individuals who previously had mild to moderate SARS-CoV-2 infection are relevant for generating data in a population that is non-severely affected by the disease, and who may suffer from sequelae that are yet to be explored, with the intention to assist in the planning of rehabilitation programs.

As is known, age and metabolic disorders are factors related to poor prognostic of the COVID-19 disease. Our idea will be to study a sub-population that exhibits low risk of severe COVID-19 disease, and that in general will be not admitted to the hospital in intensive care. However, the consequences of infection during the long term were never studied.

Our main objective is to evaluate if physical activity levels and the number of adipose tissue depots are determinants of systemic inflammatory response and general clinical functions in adults who previously suffered from mild to moderate COVID-19, before and after specific vaccination, using a cohort prospective observational study. Additionally, we will explore modulatory effects of physical activity on immune responses to the virus, focusing on the function and metabolism of peripheral blood mononuclear cells (PBMCs) after in vitro exposure to homologous serum and/or recombinant coronavirus.

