### 2.10. Sample Size Estimation and Planning for Data Analysis

A Cohort of participants previously infected with SARS-CoV-2 and age-matched healthy participants will be randomly selected from the target population. Sample size calculation (G*Power, version 3.0; power = 0.80; α level = 0.05; medium-size effect) provided an estimated 75 participants. Therefore, 100 male and female participants aged 20–40 years will be recruited (over-recruitment compensates for dropouts during follow-up).

Participants will be stratified based on habitual physical activity levels (assessed by accelerometry-low versus normal physical activity levels), body composition (normal weight versus overweight or obese), and SARS-CoV-2 status (positive versus negative). In addition, a sub-analysis will be stratified based on sex (men vs. women).

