## 3. Discussion

This protocol describes an ambitious follow-up study that will be conducted in adults previously infected with COVID-19 (before and after vaccination program), highlighting long-term consequences of COVID-19 and its correlation with physical activity, body composition, and cross-linked with vaccination in the Brazilian population. Our hypothesis links reduced visceral adipose tissue deposits (which exhibit an anti-inflammatory profile, as hypoleptinemia and hyperadiponectinemia) with higher physical activity levels as central factors in reducing the severity of SARS-CoV-2 aggression, promoting metabolic programming of immune cells (favoring anti-inflammatory response), protecting the cardiovascular system, and general clinical profile.

Patients with COVID-19 who were consistently inactive and malnutrition had a greater risk of hospitalization, admission to the ICU, and death due to COVID-19 compared with patients who were consistently meeting the minimum physical activity guidelines (150 min/week) [27,47,48]. Longitudinal cohort studies of individuals who developed severe COVID-19 are being conducted to investigate possible symptoms and long-term clinical and functional alterations [49,50]. Longitudinal follow-up studies reporting persistent symptoms and sequelae of COVID-19 in mild and moderate patients are also needed in order to understand the intrinsic physiological mechanisms involved in these processes, their potential protective factors, and public health policies needed for treatment in the post-pandemic period in order to substantially minimize long-term chronic sequelae.

In addition to investigating an overlooked population, one advantage of the study proposed here is that we will conduct comprehensive symptom and clinical assessments of long-COVID manifestations pre- and post-vaccination. Potential limitations include the fact that we will rule out the presence of current re-infection based only on the absence of clinical signs and symptoms, rather than on the basis of a negative RT-PCR test. We will also only assess a specific, young population.

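### The visceral-fat grouping rule cannot be applied as written, and the body-composition factor in the analysis section is weight class, not the adipose exposure named in the objective and hypothesis

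*Protocol article*

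**What the plan says.** The protocol article describes body composition as an exposure in four ways.

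- **Section 2.2 (Assessment Schedules)** groups participants by ultrasound visceral thickness: "Participants will be grouped into those with low-visceral adipose tissue (values below 3 ± 1 cm) and those with high-visceral adipose tissue", with the high group set at above 5 ± 1 cm. It names no middle group, gives no exclusion rule and does not explain the ± 1 cm. It also says that measurements will be expressed in absolute and percentage terms, and it collects DXA body composition including the trunk.
- **The Abstract and section 2.10** use weight class. The Abstract says that, from baseline information, "participants will be grouped based on physical activity levels (sedentary versus active), body composition (normal weight versus overweight or obese"). Section 2.10 repeats the factor as "body composition (normal weight versus overweight or obese"). Neither gives a cut-off or mentions the visceral-fat groups.
- **Section 2.1** plans to correlate serum and early cardiovascular markers with body fat and activity, without saying which fat measure.
- **The objective and hypothesis** are about adipose tissue. The Background asks whether "physical activity levels and the number of adipose tissue depots are determinants of systemic inflammatory response", and the Discussion opens its hypothesis with "Our hypothesis links reduced visceral adipose tissue deposits".

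No section says which grouping is the analysis factor, or how the visceral-fat and weight-class groups relate.

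**The concern.** Adiposity is one of the two exposures in the main objective, and two things go wrong with it.

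First, a cut-point assigns each value to one side, and a limit that carries ± 1 cm does not do that. Two analysts given the same ultrasound data could form different low and high groups, and both could claim to have followed section 2.2.

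Second, the factor listed for analysis is not the exposure in the objective. Weight class does not separate fat from lean mass or visceral from other fat. A result for normal weight versus overweight or obese would not directly answer a question about visceral fat. If section 2.2 supplies the factor, the groups are undefined over part of the range. If section 2.10 supplies it, the groups are defined but address a different exposure.

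**Working it through.** **The plan's own figure.** The only computable figure nearby is the sample size: "Sample size calculation (G*Power, version 3.0; power = 0.80; α level = 0.05; medium-size effect) provided an estimated 75 participants", with 100 recruited. No test, number of groups or correlation is given, so 75 cannot be reproduced uniquely. The step to 100 is consistent with a 25% dropout allowance: 75 / (1 − 0.25) = 100. This point does not dispute either number. The stated reason for over-recruiting is dropout, not participants who fall in no group.

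**What the rule assigns.** Let L be the lower limit (low group: value < L) and U the upper limit (high group: value > U). Section 2.2 gives L = 3 ± 1 and U = 5 ± 1. The unassigned width is U − L.

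| Reading | L (cm) | U (cm) | Unassigned band | Width (cm) |
|---|---|---|---|---|
| Face value | 3 | 5 | 3–5 | 2 |
| Inner limits | 3 + 1 = 4 | 5 − 1 = 4 | none (only exactly 4) | 0 |
| Outer limits | 3 − 1 = 2 | 5 + 1 = 6 | 2–6 | 4 |
| Both down | 2 | 4 | 2–4 | 2 |
| Both up | 4 | 6 | 4–6 | 2 |

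The gap and the meeting of the limits at 4 cm come from different readings and do not occur together. Only values below 2 cm or above 6 cm get the same assignment under every reading. This step needs no assumption.

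**How many might be affected (assumption only).** The documents give no mean, SD or shape for visceral thickness. Assume a normal distribution with mean m and SD s. The share at 3–5 cm is Φ((5 − m)/s) − Φ((3 − m)/s).

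- m = 4, s = 1: Φ(1) − Φ(−1) = 68%
- m = 4, s = 1.5: Φ(0.667) − Φ(−0.667) = 49.5%
- m = 5, s = 2: Φ(0) − Φ(−1) = 34%
- m = 6, s = 1.5: Φ(−0.667) − Φ(−2) = 23%
- m = 6, s = 1: Φ(−1) − Φ(−3) = 16%

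With means of 3–5 cm and SDs of 1–2 cm the range is 34–68%. With means of 3–6 cm and SDs of 1.5–2.5 cm it is 23–50%. Over means of 3–6 cm and SDs of 1–2.5 cm together, the lowest value is the 16% corner. The share at 2–6 cm, where membership depends on the reading, is 62–95% in the first grid and 45–82% in the second.

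**Factor against exposure.**

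| Place | Body-composition variable |
|---|---|
| Main objective (Background) | adipose tissue depots |
| Hypothesis (Discussion) | visceral adipose tissue |
| Section 2.2 grouping | ultrasound visceral thickness, two groups |
| Section 2.1 correlation | body fat, measure not named |
| Abstract and section 2.10 factor | weight class, two groups |

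The variable in the analysis section is the one that does not measure adipose tissue.

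**The case against.** The strongest reply is that section 2.10 and the Abstract agree on weight class, which is exhaustive. Section 2.2 is a measurement section and never says that its groups enter the ANOVA. This stands, and it limits the point: the gap affects the visceral-fat grouping only. A reader might infer that many participants drop out of the planned analysis. The documents do not support that, because the weight-class factor loses nobody and no visceral-fat distribution is given. The reply does not explain why the analysis factor differs from the exposure in the objective.

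It can also be said that omitting the middle may be a deliberate extreme-groups contrast, and that this is not necessarily wasteful. That is fair on information. In a linear normal model, comparing two symmetric tails of share p keeps 2φ(z)²/p of the information on the slope. For m = 4, s = 1.5 and limits of 3 and 5, z = 0.667, p = 0.2525 and φ(z) = 0.319, so 2 × 0.319² / 0.2525 ≈ 0.81. A median split would keep 2/π ≈ 0.64. So the share unassigned should not be read as the share of information lost. But section 2.2 says participants will be grouped and mentions no omitted middle.

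Two further inferences go beyond the text. One is that trained people will be misclassified as high-fat. The weight-class group is not labelled high-fat, no cut-off is stated, and the well-trained participants belong to the in-vitro sub-study. The other is that groups will be formed after outcomes are seen. The Abstract ties grouping to baseline information.

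Finally, cut-offs are often left to a full protocol or SAP. That would answer a missing cut-off. Here a rule is stated and does not work, and two stated groupings are not reconciled.

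**Conclusion.** The point holds in limited form, as a should-fix. Two parts rest on the text alone. The visceral-fat limits leave an unassigned band of 0 to 4 cm depending on how ± 1 is read. The weight-class factor in the analysis section does not match the adipose exposure in the objective and hypothesis, and no section reconciles them.

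The size in participants is not established. The figure of roughly a quarter to two-thirds at 3–5 cm, with 16% at one corner, depends entirely on assumed normal distributions. On the 4/4 reading practically nobody is left out. The defect is graded below must-fix because the factor listed for analysis has no gap and the repair is mainly wording.

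**What to change.** Name one body-composition exposure, in the same terms, in the Abstract, section 2.2 and section 2.10, and make it match the objective. The preferred choice is ultrasound visceral thickness, or DXA trunk fat, entered as a continuous covariate for all participants. This extends the body-fat correlation already planned in section 2.1, needs no cut-point and leaves nobody unassigned. Keep weight class as a secondary or sensitivity grouping.

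If visceral-fat groups are kept, replace the ± 1 limits with one exact, exhaustive cut-point. Alternatively, state exact lower and upper limits and what happens to values between them. Fix the rule before outcomes are examined.

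The cost is wording in three places and no new measurement. The one downside is that the functional form of the continuous covariate must be checked, for example linear against a spline.

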### 2.3. Blood Collection and Analysis

At each time-moment, participants will visit the laboratory after overnight fasting. Forty milliliters of blood from an antecubital vein will be collected in a tube containing EDTA. To detect previous SARS-CoV-2 infection, a lateral flow test for IgM and IgG antibodies will be performed using internal anti-SARSr-CoV IgG and IgM ELISA kits. All patients (infected and non-infected with SARS-CoV-2) will be evaluated before (without vaccine) and after (with vaccine) the vaccination program. We plan to follow up the calendar vaccination of the São Paulo Government and recruit patients according to this schedule. Please, access information about the São Paulo State vaccination calendar in the link (https://www.prefeitura.sp.gov.br/cidade/secretarias/saude/vigilancia_em_saude/doencas_e_agravos/coronavirus/index.php?) (accessed on 5 January 2021). Phenotypes of immune cells will be characterized using multicolor flow cytometry, and monocytes, T cells, and Natural Killer (NK) cell subsets in whole blood will be quantified and characterized. T lymphocytes will be identified based on their positivity for CD3 and typical light scatter. Among positive CD3 cells, CD4^+^ T and CD8^+^ T cell subsets will be quantified. Based on the expression of CD14 and CD16, the classical (CD14++CD16−), intermediate (CD14++CD16+), and non-classical (CD14^+^CD16^++^) monocytes will be quantified. The NK cells will be defined as CD3^−^CD56^+^, and the two major subsets of NK cells, CD56^hi^CD16^−^ (CD56^bright^) and CD56^lo^CD16^+^ (CD56^dim^), will be identified. Biochemistry assays, including measurements of non-ester fatty acid (NEFA), glucose, triacylglycerol, total cholesterol, and HDL-c will be analyzed using a colorimetric method. Cortisol, insulin, and apolipoprotein A1 concentrations will be analyzed using ELISA. To determine the inflammatory status of the participants, the plasma concentrations of IL-1β, IFN-α, IFNγ, TNF-α, MCP-1, MIP-1β, IL-8, IL-10, IL-12p70, IL-17A, IL-18, IL-23, IL-33, IL-1ra, IL-2, IL-6 will be measured using the LUMINEX method.

An in-vitro analysis will be conducted to determine the mechanisms underlying the immune and inflammatory responses to the SARS-CoV-2 virus as a function of physical fitness. Well-trained and age-matched non-trained controls negative for SARS-CoV-2 will be recruited as detailed in the methods section. Phenotypic characteristics of monocytes, T, and NK cell subsets in blood samples will be measured as described above. Whole blood will be stimulated with recombinant human coronavirus to determine the cytokine profile. PBMCs from well-trained participants will be collected and treated with homologous serum (from the main study collected both before and after vaccination) and recombinant coronavirus (inactive virus). PBMCs will be examined after a 24 h culture period to measure phagocytosis and production of cytokines and H_2_O_2_. *ACE-2*, *AT1R*, *AT2R*, *MASR*, *TLR-3*, *TLR-4*, *NOS*, *CETP*, *L-CAT*, and *ABCA1* gene expression will be analyzed using qRT-PCR and metabolic analysis will be conducted using Respirometry (Seahorse).

The following sub-tasks will be implemented, as described:

**T1**: Stimulation with recombinant coronavirus: Whole blood samples from each participant will be divided into two tubes. Ten milliliters will be incubated with 100 µL of PBS and, 10 mL will be incubated with recombinant human coronavirus 229E (MyBiosource^®^) [29]. Samples combined with either PBS or human coronavirus 229E will be agitated for 120 min at room temperature. After this, the serum will be extracted by centrifugation at 690× *g* for 15 min at 4 °C, aliquoted, and stored at −80 °C for later use. Concentrations of IL-1ß, IL-2, IL-4, IL-6, IL-8, IL-10, IL-17, INF-γ, and TNF-α will be determined in non-stimulated (PBS) and stimulated (coronavirus 229E) samples using the Luminex method.

**T2:** PBMC culture and Cytokine Production: 30 mL of heparinized blood will be collected from both groups (well-trained and non-trained). PBMCs will be isolated from whole blood using the density gradient technique (Ficoll, d: 1.077, Sigma). Cytokine production will be measured separately using 1 × 10^5^ cells, which will be incubated in 96 Well plates containing RPMI 1640 medium enriched with 2 mM glutamine, 50% homologous serum (from patients in the main study), or human coronavirus 229E or vehicle solution as previously described [29]. After 48 h of incubation, the concentrations of IL-1ß, IL-2, IL-4, IL-6, IL-8, IL-10, IL-17, INF-γ, TNF-α will be measured using the Luminex method.

**T3:** Analysis of Angiotensin-Converting Enzyme in PBMC: *ACE-2*, *AT1R*, *AT2R*, *MASR*, *TLR-3*, *TLR-4*, *NOS*, *CETP*, *L-CAT*, and *ABCA1* expression will be measured using qRT-PCR, as previously described [30].

**T4**: Metabolic Analysis in PBMCs using Respirometry (Seahorse): samples will be plated in a 96-well xFe96 plate (Agilent) at three different densities. The density that best responds to the test will be used for subsequent experiments. For extracellular acidification (ECAR) studies, the Glycolytic Stress assay will be used. The drugs, 2-deoxyglucose, oligomycin, and acute glucose, will be used. To measure the consumption of mitochondrial oxygen (OCR), the MitoStress assay will be performed using the drugs oligomycin, CCCP (Carbonyl cyanide m-chlorophenylhydrazone), rotenone, and antimycin. The concentrations of all drugs will be standardized for better trial performance. All analysis will be done using Seahorse XF96 Extracellular flux Analyzer.

